**Engagement outcomes**						
	**Patient engagement**		Noom		Weekly	
		Number of dDPP^a^ log-ins	Noom		Weekly	
		Number of dDPP lessons completed	Noom		Weekly	
	Perceived provider involvement with dDPP progress		Patient portal 1-item survey		3, 6, 9, and 12	

^a^dDPP: digital diabetes prevention program.

Changes in body weight will be our primary weight-based outcome. Second, we will assess the achievement of a 7% weight loss goal (the DPP weight goal). Weight will be collected from a Bluetooth-linked wireless weight scale, a validated process that automatically reports weigh-ins to the dDPP platform server [6,44-46]. In addition to providing the scale and weight measurement protocol, regular checks of weight data by research staff will be conducted to identify and follow up on values that appear invalid and comparisons with EHR-based data from clinical visits during the study period. Physical activity will be assessed using validated accelerometers or pedometers integrated into the dDPP platform [47-50]. A_1c_ will be assessed using home A_1c_ devices, which have been shown to be safe and equivalent to laboratory testing and are increasingly used in pragmatic digital studies to avoid unnecessary burden on participants [44,51,52].

Patient engagement in the dDPP will be measured using data on log-ins, lesson completion, feature interactions, and messages with coaches and social groups. These data will be reported at regular intervals from the dDPP using a secure application programming interface. Perceptions of engagement will be assessed at both patient and provider levels via a survey at 6- and 12-month intervals. To assess the determinants, process, and outcome measures associated with our theoretical model (capability, opportunity, motivation, ease of use, and usability) and relevant implementation outcomes (acceptability, adoption, cost, and sustainability), patients and providers will be asked to complete the surveys outlined in phase 2, with applicable modifications as identified through phase 2 design review and optimization. Data collection will occur at study enrollment (baseline) and 6- and 12-month intervals.

#### Data Analysis

All data will be descriptively summarized using frequencies and percentages for categorical variables and means and SDs for normally distributed data or median and IQR for skewed continuous variables. All available data will be included in data listings and tabulations with the number of missing values indicated. All analyses will follow the principle of intention-to-treat. Before analyzing the data, we will compare drop-out and missing data across study arms to assess whether any patient characteristics were associated with the missing data and, if necessary, perform additional analyses using multiple imputation methods.

The primary clinical outcomes (weight reduction or BMI, physical activity, and A_1c_) will first be analyzed as continuous variables using generalized estimating equation (GEE) models. Each GEE model will include a categorical indicator variable for the randomized study arm (control as reference), a variable corresponding to measurement time (baseline as reference), and an interaction term of the 2 variables. We will explore adjusting for any baseline demographics, use behavior, and survey responses that may be unbalanced between study arms. A Bonferroni-Holm correction method for multiple comparisons will be used to control the type I error rate of 0.05. A similar GEE model with a logit link function will be used to analyze the achievement of a 7% weight loss as a binary dependent variable.

We will also explore the extent to which engagement with the program acts as a mediator. We propose using a single mediator causal model approach with bootstrap-derived confidence intervals to measure the intervention’s effect on weight loss, physical activity, and A_1c_ through the specific mechanism of patient engagement.

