### Digital Health Engagement: Challenges for Patients and Providers

Despite the popularity and effectiveness of digital health interventions such as dDPPs, the integration of these tools into clinicians’ armamentaria for disease management and healthy behavior change has been limited [10]. The reasons for this include technical barriers, suboptimal user experience, entrenchment of practice habits and preferences, perceived administrative burden, and unfavorable reimbursement environments. In particular, user engagement in digital health tools represents a critical, but challenging, component of the effective translation of evidence-based behavioral interventions into pragmatic, scalable digital solutions [11,12]. Although regular interaction with digital health tools for weight loss and diabetes prevention has been shown to improve targeted health outcomes with a tendency toward a dose-response relationship [13-15], low rates of long-term engagement are known barriers to achieving and maintaining these outcomes [16-18]. Tools to identify and measure engagement have been lacking, in part, because of the lack of conceptual clarity and precision in defining the features of engagement, and gaps remain in the understanding of the links between specific engagement behavior and the achievement of target health goals [19-21]. For providers, poor integration of dDPPs into the existing health information technology (HIT) and electronic health record (EHR) workflows negatively impacts the ability to incorporate relevant aspects of the programs into patient care, communication, or education. This results in missed opportunities for comprehensive care delivery in diabetes prevention, as providers are unable to overcome barriers in technology, workflows, and competing priorities to effectively leverage digital health tools. Integrated clinical tools that can facilitate patient-provider interaction around dDPPs may contribute to improved patient engagement and adherence to these programs and improved health outcomes by addressing some of these issues.

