### Objectives

Few studies have investigated integrating consumer-facing digital health programs such as dDPP platforms into existing clinical systems, such as the EHR, or into clinical workflows of ambulatory care practices to facilitate patient-provider interaction with these tools. We hypothesize that existing digital technology, such as text messaging systems, patient portals, and EHR integrations, can support both clinicians and patients by improving communication, education, and shared decision making around digital behavior change tools. The purpose of this study is to design and test a novel clinical tool to enhance engagement with digital behavior change efforts in diabetes prevention.

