### dDPP Platform: Noom

Our study (NCT04049500) will use the commercially available application Noom to provide patients with a dDPP platform. Noom is a mobile health behavior change lifestyle app based on the CDC’s DPP that allows users to log their meals, weight, and exercise and physical activity minutes. Noom connects users with an individual behavior change coach and support group and provides a DPP curriculum through daily articles that cover topics including diet, exercise, and healthy behavior psychology. The core philosophy of Noom is to work with the user to adopt a healthier lifestyle in a way that best fits the user’s individual life. Preliminary studies of Noom showed high levels of effectiveness and acceptability compared with in-person DPPs. In overweight or obese adults with prediabetes, participation in Noom was associated with significant weight loss at 24 and 65 weeks, which exceeded the CDC DPP 5% weight loss requirement [7,32]. In one study, participants exhibited a dose-dependent response with greater mean weight loss at 65 weeks in those who engaged more in the program [32]. In addition, certain metrics of in-app engagement such as weekly logged meals, weigh-ins, and group posts were shown to predict weight loss [32]. Noom is a well-established commercial dDPP platform with a growing market share and considerable brand recognition and robust customer and technical support.

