#### Setting and Participants

The study trial will use a practice-level cluster-randomized design, with 1:1 randomization of 40 primary care practices resulting in 20 clinics per study arm. Randomization will be stratified by clinic size to ensure even distribution of different-sized clinics to the two study arms. The proposed sample size provides 80% power to detect a 30% increase in dDPP session completion and a 2 kg increase in 12-month weight loss in the intervention arm relative to the control. This calculation assumes 20% attrition, two-sided tests with a type I error rate of 0.05, and an intraclass correlation coefficient of 0.05.

We will recruit patients who meet the inclusion criteria with primary care providers at the study sites through the patient portal, an increasingly common and effective approach for recruitment [41-43], and through population-based outreach from NYULH prediabetes registries with assent from primary care providers. Intervention participation will last 12 months.

Patients enrolled in the intervention arm will receive access to the dDPP platform and the engagement system developed and refined in phases 1 and 2. Patients in the control arm will receive the dDPP alone. Providers in both arms will receive information on the study and educational material for their patients. Patients will receive enrollment and onboarding information and training for dDPP, the engagement system, and the home devices (weight scales and pedometers or fitness trackers), as outlined and refined in phase 2. In addition to the home devices, upon enrollment, patients will be provided a home A_1c_ testing kit and instructions for its use for the study.

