**Clinical outcomes**						
	Weight reduction (kg)		Noom (via a wireless scale)		Baseline, 6, and 12	
	Physical activity (steps per day)		Noom (via a wireless pedometer)		Baseline, 6, and 12	
	A_1c_ (%)		A_1c_ home test kit		Baseline, 6, and 12	

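### Weights reach the trial only through weigh-ins on the platform whose use the intervention aims to raise, so making imputation conditional and secondary leaves the main weight contrast open to bias of unknown size and direction

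*Protocol article*

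**What the plan says.** All references are to the protocol article.

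- **Source of weight.** Table 1 (Phase 3 study outcomes) gives the source as "Noom (via a wireless scale", at baseline, 6 and 12 months. The text after the table says that the scale "automatically reports weigh-ins to the dDPP platform server".
- **Checks on weight.** The same text provides a weight measurement protocol, staff follow-up of values that look invalid, and "comparisons with EHR-based data from clinical visits during the study period". It does not describe any of these as replacing a weight that is absent.
- **Aim of the intervention.** The Objectives section describes a tool "to enhance engagement with digital behavior change efforts in diabetes prevention". The phase 3 Setting and Participants section claims "80% power to detect a 30% increase in dDPP session completion and a 2 kg increase in 12-month weight loss", assuming 20% attrition.
- **Link to outcome.** The section on the Noom platform reports that certain metrics of "in-app engagement such as weekly logged meals, weigh-ins, and group posts were shown to predict weight loss". The Introduction adds that "low rates of long-term engagement are known barriers to achieving and maintaining these outcomes".
- **Analysis.** The phase 3 Data Analysis section fixes a GEE with arm, time and their interaction, under intention-to-treat. Drop-out and missing data are first compared between arms and examined against patient characteristics. The team will then "if necessary, perform additional analyses using multiple imputation methods".

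**The concern.** Stepping on the connected scale produces the outcome. By the article's own account it is also an engagement behaviour that predicts the outcome, and engagement is what the randomized intervention tries to change. A model with only arm, time and their interaction, fitted without weights to observed records, generally needs missingness to be unrelated to weight once arm and time are known. The article's own theory makes that doubtful.

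The planned safeguard does not meet the problem. Comparing drop-out by arm and by patient characteristics uses observed quantities, so it cannot show whether missingness depends on weights nobody saw. No criterion for necessity is given. Even when imputation is triggered it is additional, so the headline estimate would still be the unimputed one.

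At stake is whether the 12-month weight contrast estimates the effect in everyone randomized, or a mixture of that effect and a change in who continues to weigh in.

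**Working it through.** **1. The plan's own figure.** The stated design is 40 practices (20 per arm), a 2 kg difference, 80% power, two-sided 0.05, ICC 0.05 and 20% attrition. The article gives neither the SD of weight change nor the number of patients per practice, so the power can be neither confirmed nor refuted. Assuming an SD, the effective number per arm is n = 2(1.96 + 0.84)² SD² / 2². Completers per practice are n(1 − 0.05) / (20 − 0.05n), and enrolment is that number divided by 0.8.

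| Assumed SD (kg) | n per arm | Enrolled per practice | Total |
|---|---|---|---|
| 5 | 99 | 7.8 | about 310 |
| 6 | 142 | 13.1 | about 520 |
| 7 | 193 | 22.1 | about 890 |
| 8 | 252 | 40.4 | about 1,620 |

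**2. What missing weights do to the contrast.** Let m be the share missing in an arm, and k the number of kg by which the missing lost less than the observed. The observed mean loss is the full mean plus m·k, so with a true difference of 2 kg:

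observed contrast = 2 + m(I)·k(I) − m(C)·k(C)

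The article gives none of the arm-specific m or k. Every value below is an assumption.

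| Missing C / I | Shortfall C / I (kg) | Observed contrast (kg) |
|---|---|---|
| 25% / 15% | 2 / 2 | 2 + 0.3 − 0.5 = 1.8 |
| 25% / 15% | 4 / 4 | 2 + 0.6 − 1.0 = 1.6 |
| 30% / 10% | 2 / 2 | 2 + 0.2 − 0.6 = 1.6 |
| 30% / 10% | 4 / 4 | 2 + 0.4 − 1.2 = 1.2 |
| 20% / 20% | 4 / 2 | 2 + 0.4 − 0.8 = 1.6 |
| 20% / 20% | 2 / 4 | 2 + 0.8 − 0.4 = 2.4 |

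The last two rows bear on the trigger. Drop-out is identical in the two arms, yet the contrast is wrong by 0.4 kg, in either direction.

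**3. A milder, more structured model.** Engagement is standard normal in control and shifted upward in the intervention arm. The probability of a recorded weight rises with engagement by the same rule in both arms. Overall missingness is 20%. Across slopes of 1 to 3 kg per SD of engagement, log-odds slopes of 0 to 1.5 and shifts of 0 to 0.5 SD:
- bias is zero if weighing in does not depend on engagement, or if engagement does not differ by arm;
- otherwise bias runs from −0.01 to −0.27 kg, towards no effect. The largest value has 24% missing in control and 16% in intervention.

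**4. Simulation.** There were 150 trials of 40 practices with 15 patients each: SD 6, ICC 0.05, true difference 2.00 kg, slope 2 kg, log-odds slope 1, shift 0.5. Average missingness was 24% in control and 17% in intervention.

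| Analysis | Estimate (kg) | Monte Carlo SE |
|---|---|---|
| Full data | 1.99 | 0.05 |
| GEE on observed weights | 1.88 | 0.08 |
| Observed change scores | 1.87 | 0.05 |
| Imputation from engagement, within arm | 2.00 | 0.05 |

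The GEE figure alone is imprecise, but the large-sample model in step 3 gives −0.11 kg for the same inputs. Imputation recovers the truth here because engagement is the only driver of missingness in this simulation.

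**5. Effect on power.** Take SD 6 and n = 142, so that power is 80% at 2 kg. Power is Φ(d / (6√(2/142)) − 1.96). For d = 1.8, 1.6 and 1.2 kg this is 72%, 61% and 39%.

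**The case against.** Five points can fairly be made for the plan.

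- **Bias is not demonstrated.** A reader might infer that the design makes bias certain, or that it runs against the intervention by a known amount. The documents support neither. They give one attrition figure, with no split by arm, and no slope of weight on engagement. Bias can be zero, and under a mechanism common to both arms it is modest. This stands in full.
- **Observed-only GEE is an inference.** The reference to all available data concerns listings and tabulations, and the article does not say which records enter the model. It is still the natural reading when imputation is called additional.
- **Detail belongs in an analysis plan.** The imputation model, visit windows and sensitivity parameters may well sit in a document not shown, and their absence is not criticised here. What remains is a rule the article does state: GEE first, with imputation secondary and dependent on a look at the data.
- **The capture route is lighter than full app use.** The scale reports automatically, so the outcome needs a weigh-in on a connected scale at three time points, not continuing lessons or log-ins. That weakens the link to engagement without breaking it, since weigh-ins are themselves listed as an engagement metric. Staff follow-up is described for implausible values, not for absent ones.
- **EHR weights are not a clean rescue.** They come from clinical visits, and the intervention has a provider-facing part, so their availability may also differ by arm. This stands and limits how they should be used.

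**Conclusion.** The point holds as a weakness in a stated analysis choice. It is not an arithmetic error. Missing 6- and 12-month weights are likely to be informative and may differ by arm, so a GEE on observed weights can bias the contrast. The planned drop-out comparison can neither exclude this nor settle whether imputation is needed.

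Size and direction are unknown, and every kg figure above is hypothetical. For a true 2 kg effect, the 25% versus 15% example gives 1.8 to 1.6 kg. The common-mechanism model at 20% missing gives a loss of at most about 0.27 kg. Unequal shortfalls can move the contrast either way. The conclusion rests on two readings: that the GEE uses observed weights only, and that weighing in behaves like the other engagement measures.

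The 7% weight-loss outcome uses the same weights, and daily steps also arrive through Noom, so both share the exposure. A1c comes from a home kit and does not share this route.

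**What to change.** **Change.** Make multiple imputation, or a weighted GEE, the main analysis whatever the drop-out comparison shows. Carry it out by arm, respect clustering by practice, and use earlier weights and the weekly log-in and lesson data already planned. Keep the drop-out comparison as description.

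**Sensitivity analyses.** Retain the GEE on observed weights, and add a delta-adjusted analysis in which missing patients are assumed to have lost less weight than imputed, with the shift allowed to differ by arm.

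**EHR weights.** Use them as auxiliary information in the imputation or in a sensitivity analysis, not as a direct replacement for missing scale weights. A source indicator would deal with different scales but not with selection through clinic attendance.

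**Cost.** No new data collection is needed. The price is more analysis work and dependence on an imputation model. The article does not say that the engagement data will be complete for every patient, so the model must allow for gaps in them. Imputation from engagement also cannot remove dependence on weight that engagement does not explain, which is why the delta-adjusted analysis is needed.

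### The phase 3 GEE contrasts change from baseline and omits the clinic-size stratum: valid, but usually less precise than a prespecified baseline- and stratum-adjusted model

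*Protocol article*

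**What the plan says.** Protocol article, Phase 3: RCT, Data Analysis, on weight or BMI, physical activity and A1c as continuous outcomes: "Each GEE model will include a categorical indicator variable for the randomized study arm (control as reference"), together with "a variable corresponding to measurement time (baseline as reference), and an interaction term of the 2 variables". Further adjustment is left open: "We will explore adjusting for any baseline demographics, use behavior, and survey responses that may be unbalanced between study arms". Neither the baseline value of the outcome as a covariate nor clinic size is named.

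Phase 3: RCT, Setting and Participants: the design is "1:1 randomization of 40 primary care practices resulting in 20 clinics per study arm", and "Randomization will be stratified by clinic size to ensure even distribution of different-sized clinics to the two study arms".

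Table 1 schedules weight, steps and A1c at baseline, 6 and 12 months. The baseline values are therefore collected, and clinic size has to be known in order to randomize.

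**The concern.** Baseline is treated as one of the responses, and the arm term lets the two arms have different baseline means. The arm-by-time term then equals the difference between arms in mean change. Under randomization, an analysis of the follow-up values with baseline as a covariate estimates the same effect, and usually with smaller variance.

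Clinic size restricts the randomization but plays no part in the analysis. If clinic size predicts change, the reported standard error is larger than the true sampling error.

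At stake is power, chiefly for A1c and steps. The article lists both among the primary clinical outcomes under a Bonferroni-Holm correction, but its power statement does not cover them. In addition, the only adjustment offered depends on imbalance seen in the data, which is harder to defend than covariates fixed in advance.

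**Working it through.** **1. The plan's own figure.** The article states 80% power for "a 2 kg increase in 12-month weight loss in the intervention arm relative to the control". On the assumptions: "This calculation assumes 20% attrition, two-sided tests with a type I error rate of 0.05, and an intraclass correlation coefficient of 0.05". It gives neither the SD nor the number of patients per practice, so the 80% can be neither reproduced nor refuted. Let n be the patients per arm needed without clustering and m the analysed patients per practice. Setting 20m / (1 + 0.05(m − 1)) = n gives m = 0.95n / (20 − 0.05n).

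- Assumed SD of change 4 kg: n = 63, m = 59.85 / 16.85 = 3.55, and 40 × 3.55 / 0.8 ≈ 178 enrolled.
- Assumed SD of change 8 kg: n = 252, m = 239.4 / 7.4 = 32.35, and about 1,618 enrolled.

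Practice size could therefore plausibly lie anywhere from about 3.5 to 32 analysed patients, which matters in step 3.

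**2. Independent patients, equal variances at both times.** Let rho be the baseline/follow-up correlation (assumed; not in the article). The variance of the change contrast is proportional to 2(1 − rho) and that of the baseline-adjusted contrast to 1 − rho². The ratio is (1 + rho)/2. The last column starts from exactly 80% power for the change contrast.

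| rho | variance ratio | power after adjustment |
|---|---|---|
| 0.5 | 0.75 | 89.9% |
| 0.7 | 0.85 | 86.0% |
| 0.9 | 0.95 | 82.0% |
| 0.95 | 0.975 | 81.0% |

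A simulation (40 practices of 10 patients, ICC 0.05, practice effects correlated over time to the same degree as patient effects) gave ratios of 0.73-0.77, 0.83-0.85 and 0.97-0.98 at rho 0.5, 0.7 and 0.95. The arm-by-time coefficient equalled the difference in mean change.

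**3. Practices as the randomized unit.** Take total variance 1, ICC 0.05, patient-level correlation 0.5 and practice-effect correlation over time c. The variance of a practice mean is then:

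- Change: 2(0.05)(1 − c) + 2(0.95)(0.5)/m.
- Adjusted for the patient's baseline only, with pooled slope b = 0.05c + 0.475: 0.05(1 − 2bc + b²) + 0.95(1 − b + b²)/m.

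With c = 1 and m = 32, b = 0.525. Change gives 0.95/32 = 0.0297. Adjustment gives 0.05 × 0.2256 + 0.95 × 0.7506/32 = 0.0113 + 0.0223 = 0.0336. The ratio is 0.0336/0.0297 = 1.13, so adjustment is worse here. At c = 1 the same formulas give 0.87 for m = 10 and 0.99 for m = 20. At c = 0.5 they give 0.75 for every m.

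**4. Adding the practice-mean baseline.** The ratio becomes (1 + r)/2, where r is the correlation between baseline and follow-up practice means. In the adverse case (c = 1, m = 32), r = (0.05 + 0.475/32) / (0.05 + 0.95/32) = 0.0648/0.0797 = 0.814. The ratio is 0.91, so the reversal disappears.

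**5. Stratum.** In the same simulation, with an assumed 0.2 SD difference in change between two strata, the mean estimated standard error of the change contrast was:

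| rho | without stratum | with stratum | actual SD of the estimate |
|---|---|---|---|
| 0.5 | 0.125 | 0.121 | 0.119 |
| 0.7 | 0.098 | 0.093 | 0.090 |
| 0.95 | 0.050 | 0.038 | 0.037 |

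The estimate itself was no more variable without the stratum; only its reported standard error was too large. With clinic size unrelated to change there was no difference. Adding stratum to the stated GEE as a main effect alone left the interaction estimate unchanged (difference below 1e-14).

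**The case against.** The strongest defence is that nothing is wrong with the stated model. The article names change in body weight as its weight-based outcome and states its power for 12-month weight loss, and a baseline-referenced arm-by-time term estimates exactly that. It is a standard analysis, and an article may leave final covariates to a fuller plan. On weight, the only clinical outcome with stated power, the gain is one to two power points. The larger gains for A1c and steps rest on assumed correlations. In a cluster design, change scores remove stable practice effects that patient-level baseline adjustment removes only in part.

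Most of this stands, and it limits the point to efficiency. It does not remove it. The article writes the model out term by term and offers only imbalance-driven adjustment beyond it, so this is a stated choice and not detail left to another document. The baseline-adjusted model also targets the same arm effect. The clustering objection is met by including the practice-mean baseline.

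A reader might infer three stronger things that the documents do not support:

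- **Baseline adjustment wins whenever the correlation is below 1.** That holds for independent patients; step 3 shows a counterexample in this design.
- **Omitting the stratum invalidates the standard errors or discards the benefit of stratifying.** The balance from stratified allocation stays in the estimate, and the standard error is at most conservative.
- **The stated 80% power is wrong.** Its inputs are not given.

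**Conclusion.** The point holds as one of efficiency, not of bias or type I error. The likely gain is small for weight (2.5-5% of variance at an assumed rho of 0.90-0.95). It may reach 15-25% for A1c and steps at an assumed rho of 0.5-0.7. The upper figures need practice effects about as changeable over time as patient values; with large, stable practices the gain shrinks, and it can turn into a loss if only the patient-level baseline is used. The stratum part matters only if clinic size predicts change, which the article neither shows nor rules out. Correlation, practice stability and practice size are all assumptions here. Choosing the 12-month contrast as the primary estimate is a separate question and no part of this point.

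**What to change.** For each continuous outcome, prespecify a model of the 6- and 12-month values on arm, visit, arm-by-visit, the patient's baseline value of that outcome, the practice-mean baseline value and the clinic-size stratum, clustered by practice. Let this replace the selection of covariates by observed imbalance.

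State how patients without a baseline value are kept: either impute it, or use a longitudinal model with a baseline mean common to both arms and a stratum-by-time term. A stratum main effect added to the present GEE would not be enough.

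The cost is a few degrees of freedom among 40 practices and the extra rule for missing baselines. No new data, visits or patients are needed. The wording should be settled before outcome data by arm are seen.

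### Read naturally, the logit GEE for 7% weight loss keeps baseline as the reference visit, where no patient can be a responder, so its arm-by-time coefficients have no finite estimate; fitting follow-up visits only repairs it

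*Protocol article*

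**What the plan says.** The Data Analysis section of Phase 3 in the protocol article sets out the terms of the GEE models in one sentence. On the arm term it reads: "Each GEE model will include a categorical indicator variable for the randomized study arm (control as reference". The visit terms that go with it are: "a variable corresponding to measurement time (baseline as reference), and an interaction term of the 2 variables". Later in the same paragraph comes the responder outcome, coded yes or no: "A similar GEE model with a logit link function will be used to analyze the achievement of a 7% weight loss". Nothing there removes the baseline record or changes the reference visit for that model.

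The text after Table 1 (Procedures and Data Collection) makes change in body weight the main weight outcome and then adds: "Second, we will assess the achievement of a 7% weight loss goal (the DPP weight goal". Table 1 lists weight at baseline, 6 and 12 months.

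The trial randomizes practices: "1:1 randomization of 40 primary care practices resulting in 20 clinics per study arm". The stated power concerns other quantities, "80% power to detect a 30% increase in dDPP session completion and a 2 kg increase in 12-month weight loss"; no figure is given for the responder outcome.

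**The concern.** Taken over term by term, the model for the continuous outcomes becomes a logistic model whose reference visit contains no events and cannot contain any. A patient has lost 0% of baseline weight at baseline, so the 7% indicator is 0 for everyone in both arms. With baseline as reference, each arm-by-time coefficient compares the arm log odds ratio at a follow-up visit with the arm log odds ratio at baseline, and the latter does not exist.

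In a model of this shape the arm-by-time coefficient is the one usually read as the treatment effect. An analyst who fits the model as described and reads that line gets a number set by where the iterations stopped, with a meaningless standard error. The result for the program's own weight goal would then depend on software settings and not on the data.

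**Working it through.** The plan gives no figure for this model, so there is none to reproduce. The core of the check is algebra; a simulation shows what software returns.

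**Algebra.** Let p(a,t) be the probability of having lost 7% in arm a (0 control, 1 intervention) at month t. With three visits the model is saturated:

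- intercept = logit p(0,0)
- arm = logit p(1,0) − logit p(0,0)
- arm-by-time at t = [logit p(1,t) − logit p(0,t)] − [logit p(1,0) − logit p(0,0)]

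By definition p(0,0) = p(1,0) = 0. The intercept is therefore minus infinity, the arm effect is minus infinity less minus infinity, and each arm-by-time term contains that same undefined difference. Adding arm to arm-by-time cancels it and leaves logit p(1,t) − logit p(0,t), which is finite.

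**How fast precision is lost.** With n patients per arm and baseline probability p0, the baseline cells alone contribute √(2 / [n·p0·(1−p0)]) to the interaction standard error (independent observations). For n = 160 this is 1.12 at p0 = 0.01, 11.18 at 0.0001 and 1,118 at 0.00000001. The true p0 is 0, so there is no limit.

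**Simulated trial.** From the article: 40 practices, 20 per arm, and visits at 0, 6 and 12 months. Assumed: 8 patients per practice (160 per arm), the event rates and the within-practice correlation. Responders were:

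| Arm | Month 0 | Month 6 | Month 12 |
|---|---|---|---|
| Control | 0/160 | 30/160 | 25/160 |
| Intervention | 0/160 | 39/160 | 42/160 |

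The log odds ratios follow directly from the counts:

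- month 6: ln(39/121) − ln(30/130) = −1.132 + 1.466 = 0.334
- month 12: ln(42/118) − ln(25/135) = −1.033 + 1.686 = 0.653

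**Baseline rows kept, model as described.**

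| Fit | 12-month interaction | Its SE | SE of arm + interaction, month 12 |
|---|---|---|---|
| Logistic, 10 iterations | 0.653 | 22 | not computed |
| Logistic, 25 iterations | 0.653 | 39,816 | not computed |
| Logistic, 60 iterations | 0.100 | 7.5 million | not computed |
| GEE by practice, independence | 0.737 | missing | 0.234 |
| GEE by practice, exchangeable, 10 iterations | 1.161 | missing | 91.8 |
| GEE by practice, exchangeable, 20 or more | 0.173 | 3.9 million | missing |

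In the GEE fits arm plus interaction stayed at 0.334 (month 6) and 0.653 (month 12) throughout. Its standard error is of the right size under independence and useless under exchangeable correlation.

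**Baseline rows dropped, exchangeable GEE by practice.** The fit converges. The arm log odds ratio is 0.334 (SE 0.239) at 6 months. The arm-by-visit term is 0.319 (SE 0.313), so the 12-month log odds ratio is 0.334 + 0.319 = 0.653 (SE 0.271).

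**The gap between 0.234 and 0.271.** This is mostly rounding. The independence fit was run to a very tight tolerance, which drove the intercept to −35.4, so the contrast variance came from cancelling enormous terms. In 20 further simulated trials fitted under independence at 10 and 25 iterations, the 12-month contrast with baseline rows kept matched a fit to the month-12 records alone, with a largest SE difference of 0.00002.

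**The case against.** The strongest reply is that the article does not pin this model down. The list of terms follows a sentence about continuous outcomes, the responder model is called similar and not identical, and the article condenses a fuller plan that may restrict the model to follow-up visits. This stands in part: the authors may well intend to drop baseline. But the list is introduced as applying to each GEE, and the only departures named are the link and the outcome type. The point concerns a stated parameterisation that does not suit this endpoint, not an omitted detail.

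Second, the article never says which coefficient will be tested. That is true, and it limits the charge. An analyst who forms arm plus interaction under an independence working correlation gets a sound answer. No working correlation is stated, however, and under an exchangeable one, a common choice when practices are randomized, the contrast's standard error was missing or in the tens.

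Third, a standard error in the millions is hard to overlook, and dropping the baseline rows is a routine reaction. That stands as well, and it is a reason to rate the point low.

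A reader might infer that the 7% endpoint cannot be analysed at all. The documents do not support this, because the follow-up odds ratios are identified whether or not the baseline rows stay in.

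A reader might also infer that the continuous models fail in the same way, since weight reduction is a constant zero at baseline. They do not. In a linear GEE the interaction is then simply the difference in mean change. With complete simulated data, weight and weight reduction gave the same 12-month interaction apart from sign (1.706 and −1.706, SE 0.595 for both).

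**Conclusion.** The point holds on the natural reading of the Data Analysis section. The responder indicator is zero for everyone at the reference visit, so the intercept, the arm main effect and the arm-by-time coefficients have no finite estimate, and what software prints for them is arbitrary. This follows from the definition of the outcome and does not depend on sample size, event rate or intraclass correlation. The simulated figures rest on assumed practice size, event rates and correlation, and serve only as illustration.

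The reach is narrow. One outcome is affected, placed second to change in body weight and outside the power statement. The arm odds ratio at 6 and 12 months can still be recovered. Severity is moderate to minor: the wording should be corrected before data are analysed, so that the result does not turn on a software setting, but no main conclusion of the trial depends on it.

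**What to change.** State that the 7% weight-loss model uses the 6- and 12-month records only, with arm, visit and arm-by-visit as terms and practice as the cluster. Name the arm contrast at 12 months as the test of this outcome. The clinic-size stratum used in randomization and baseline weight may be added as covariates; both are already available, and neither is needed to cure the problem. The models for the continuous outcomes need no change on this account.

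The cost is a sentence or two in the analysis section. No extra data, visits or patients are required.
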